### Study visits

Women are recruited by the obstetrician or midwife between 6–14 weeks of pregnancy during the first routine antenatal visit. To assess bias in recruitment, eligible women who decline participation, are asked to give a limited informed consent to collect data from the electronic medical files and to fill in a short general questionnaire on socio-economic factors. Signed informed consent for participating in the study is obtained before the first visit of the study. Informed consent includes permission for gathering data from the medical records, storage of blood samples for max. 10 years for additional analyses related to the current study and for the centers participating in the sub-studies permission for the measurement of the skin fold thickness of the baby at birth and collection of cord blood.Figure 2 gives a detailed overview the different study assessments at the different visits. Study procedures at each visit (visit 1, visit 2 and visit 3) include blood collections, anthropometric measurements and self-administered questionnaires.

**Figure 2 F2:**
[figure not shown]
Overview of the different assessments in the BEDIP-N study.

#### Blood collections

Venous blood is drawn by a phlebotomist, nurse or midwife at each study visit. A fasting blood sample is drawn after a minimum of 10 hours fasting.

• For the GCT, no specific preparation is necessary. First a blood sample is collected (to later evaluate the non-fasting glycaemia), followed by a consumption of a 50 g glucose beverage (Glucomedics®) in 5 minutes and followed by a second blood sample 1 h after the intake of the glucose beverage. Data on the time of the GCT and the time of the last meal are collected.

• For the 75 g OGTT, participants are instructed to be at least 10 hours fasting and not to smoke nor engage in any physical activity during the test. They are also instructed to only drink water, but no coffee, cola or any drink containing sugar or caffeine. First, a fasting blood sample is taken, followed by a consumption of a 75 g glucose beverage (Glucomedics®) in 5 minutes. This is then followed with different blood collections at 30 minutes, 60 minutes and 120 minutes. At visit 3 women are allowed to continue breastfeeding during the OGTT and this will be recorded. The participants complete all the other study assessments during the 2-hour waiting time.

Blood samples for the analyses specifically related to the study, are in each study site processed, aliquoted and placed in a-20°C freezer within 90 min of collection. Every three months blood samples collected at the study sites are transported by a research assistant from UZ Leuven to the central laboratory of Experimental Endocrinology of the University of Leuven (KU Leuven) for longer term storage in a -80°C freezer.

#### Clinical examinations

Blood pressure (BP) is measured twice with 5 minutes interval using an automatic blood pressure monitor (Omron Philips large 34-44 cm). Height is measured to the nearest 0.5 cm using a calibrated wall-mounted stadiometer. Weight is measured using a calibrated portable Tanita HD 382 digital scale, which measures up to 150 Kg. Waist circumference is measured in centimeters by applying the tape directly on the skin, horizontally at the level laterally that is midway between the iliac crest and the lowest lateral portion of the rib cage.

At visit 1: BP, height, weight and waist circumference are measured. At visit 2b: BP and weight are measured. At visit 3: BP, weight and waist circumference are measured. BMI is calculated as weight (Kg) divided by height (m) squared.

#### Self-administered questionnaires

Table 3 gives an overview of the different questionnaires at each visit.

**Table 3 T3:** Overview of the different self-administered questionnaires at the different visits

	**Visit 1**	**Visit 2a**	**Visit 2b**	**Visit 3**
Questionnaire on general habits and socio-economic factors	**X**			
Questionnaire on lifestyle	**X**		**X**	**X**
Questionnaire IPAQ			**X**	**X**
Questionnaire on tolerance of GCT		**X**		
Questionnaire on tolerance of OGTT			**X**	
Questionnaire on depression			**X**	**X**
Questionnaire on breastfeeding/contraception				**X**
Questionnaire on general health				**X**

IPAQ: International physical activity questionnaire; GCT: glucose challenge test; OGTT: oral glucose tolerance test.

• **Questionnaire on general habits and socio-economic factors**

• We use a self-designed questionnaire to extensively collect information on family history of diabetes, smoking, alcohol and illicit drug habits, ethnic origin and education level of the participant and her parents. We also ask about marital status, employment and income.

• **Questionnaire on lifestyle**

• We use a questionnaire on lifestyle that has been previously used to question daily walking activities and servings per weeks of different important food categories and beverages [32].

• **The international questionnaire on physical activity (IPAQ)**

• The IPAQ questionnaire is a wildly used questionnaire that is also validated for use in the Belgian population and has also been used in pregnancy [33]. IPAQ extensively questions different areas of physical activity such as job-related physical activity, transportation, house work and caring for family, recreation and time spent sitting. We have added a question on the time watching television or playing computer games to better assess sedentary behavior.

• **Questionnaires evaluating tolerance of GCT and OGTT**

• We use a self-designed questionnaire to collect information on the tolerance of the different screening tests for GDM and also ask for the preference of the participants for either test.

• **Questionnaire on depression**

• The 20-item Center for Epidemiologic Studies-Depression (CES-D) has been widely used with pregnant women and postpartum women to asses depression symptoms over the past 7 days [34].

• **Questionnaire on breastfeeding and contraception**

• We use a self-designed questionnaire to extensively collect information on the duration and frequency of breastfeeding as well as on the type of contraception used.

• **Questionnaire on General health (SF-36)**

• The SF-36 health survey is used as a questionnaire on general health and has been validated for use in the maternity context [35]. Data from this questionnaire are used to calculate Qualy’s to explore the cost effectiveness of the one-step IADPSG screening strategy. The SF-36 will be obtained at visit 3 from women with previous GDM and will be send by mail to the other participants three months postpartum.

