## Background

Gestational diabetes (GDM) is a frequent medical condition during pregnancy and was historically defined as ‘any degree of glucose intolerance with onset or first recognition during pregnancy’ [1]. GDM has long been known to raise the risk of a large for gestational age (LGA) baby and macrosomia resulting in increased rates of shoulder dystocia and caesarian deliveries [2,3]. Shortly after the delivery the glucose values are generally restored to normal, but women with GDM have a seven-fold increased risk of developing type 2 diabetes (T2DM) [4]. The initial criteria for diagnosis of GDM were established more than 40 years [5]. These criteria were chosen to identify women at high risk for development of diabetes after pregnancy and not necessarily to identify pregnancies with increased risk for adverse perinatal outcome [6].

Meanwhile, two large randomized intervention trials have demonstrated improvement in perinatal outcomes in the group of women who received treatment of mild glucose intolerance during pregnancy, especially in the frequency of LGA [7,8]. Lack of international uniformity in the approach to ascertainment and diagnosis of GDM has been a major hurdle to compare the results of both studies. The ACHOIS study used a 75 g oral glucose tolerance test (OGTT) using the former WHO criteria for GDM while the study of Landon et al. used a 3-hour OGTT with the Carpenter & Coustan criteria for GDM [7,8]. Progressively more data have shown that the risk of adverse perinatal outcomes is also associated with degrees of hyperglycaemia less severe than overt diabetes during pregnancy. The ‘Hyperglycemia and Adverse Pregnancy Outcome Study’ (HAPO), showed a continuous and graded relationship between maternal hyperglycaemia and the risk for an adverse perinatal outcome, independent of other risk factors [2].

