## Methods and Design

### Study design and setting

The BEDIP-N is a national multi-centric observational and prospective cohort study with the participation of 6 centers. The University hospital of Leuven (UZ Leuven) is the coordination center.

Women are universally screened for overt diabetes and GDM during the first trimester (recruitment <14 weeks but first screening test can be delayed until max. 16 weeks) by measuring the FPG. GDM in early pregnancy is defined as a FPG ≥100 and ≤125 mg/dl (≥5.5 and ≤6.9 mmol/l), in line with the definition of prediabetes outside pregnancy [23]. Overt diabetes in early pregnancy is defined as diabetes outside pregnancy [FPG ≥126 mg/dl (7.0 mmol/l)] [23]. The IADPSG recommendation that a FPG ≥ 92 mg/dl (5.1 mmol/l) in early pregnancy be classified as GDM was not adopted since more data are necessary on its validity. Using a higher FPG cut-off for GDM in early pregnancy will allow to evaluate the number of women with a FPG < 100 mg/dl (5.5 mmol/l) in early pregnancy to later develop GDM based on the 75 g OGTT with the IADPSG criteria.

Women without diabetes or GDM in early pregnancy, will be universally screened for GDM between 24–28 weeks of pregnancy, using the 50 g GCT and independently of the result of the GCT, will all receive the 75 g OGTT. The diagnosis of GDM will be based on the 75 g OGTT with the IADPSG criteria. Participants and researchers will therefore be blinded for the result of the GCT. The result of the GCT test will later be used to evaluate the use of a GCT in a two-step approach with the use of the 75 g OGTT with the IADPSG criteria only if the GCT is abnormal. Women with GDM, will be reevaluated three months postpartum with a 75 g OGTT using non-pregnancy diagnostic criteria. Women with diabetes or GDM will be treated according to a standardized protocol in line with current routine clinical practice.Data are collected during early and late pregnancy and at delivery and for women with GDM also at three months postpartum. At each visit blood samples are collected, anthropometric measurements are obtained and self-administered questionnaires are completed. Figure 1 gives an overview of the different steps of the study.

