### Study sample

#### Study cohort

The cohort is recruited from 6 centers: UZ Leuven, the University hospital of Antwerp (UZA), Imelda hospital Bonheiden, OLV hospital Aalst-site Aalst, OLV hospital Aalst-site Asse and St Jan hospital Brussels. Five centers are situated in the Northern part of Belgium: 2 centers in the province of Flemish-Brabant, 1 center in East-Flanders and 2 centers in Antwerp. One center is situated in Brussels, the capital city of Belgium. There is a good mix between centers with an average number of women from an ethnic minority background (BME) and centers with a high percentage of women from a BME background (St Jan Hospital Brussels and OLV hospital Aalst-site Asse). UZ Leuven and St Jan Hospital Brussels have a mean number of deliveries of 2200 per year and the other centers have between 700–1000 deliveries per year.

The aim is to enroll 2563 pregnant women in the first trimester over a 2 year recruitment period (see next paragraph for power calculation). The minimum recruitment planned per center is around 175 women per year (depending on the center between 100–300 women per year) with a max. of 25% of the pregnant population that has to be recruited. Recruitment began in April 2014 and will end around October 2016.

The expected duration of the study depends on the results of the screening tests during pregnancy. If a diagnosis is made of overt diabetes in early pregnancy or if no GDM is diagnosed early or later in pregnancy, the study will end when women and the baby leave the hospital after the delivery. For these women, the max. duration of the study will be 8 months. If women are diagnosed with GDM (early or later in pregnancy), an extra visit is planned three months after the delivery. For these women the expected duration of the trial will be max. 11 months.

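### The SF-36 meant for QALYs is completed at the OGTT visit by women with GDM and by mail by all others, so a setting effect cannot be told apart from a GDM difference

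*Protocol article*

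**What the plan says.** Under Self-administered questionnaires, the protocol article gives the SF-36 a purpose: "Data from this questionnaire are used to calculate" QALYs for the cost-effectiveness aim. It then fixes the route by group: the form "will be obtained at visit 3 from women with previous GDM and will be send by mail to the other participants three months postpartum". Table 3 marks the row "Questionnaire on general health" at visit 3 only, so there is no SF-36 at visits 1, 2a or 2b in either group.

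Visit 3 is the postpartum glucose test. Study design and setting states: "Women with GDM, will be reevaluated three months postpartum with a 75 g OGTT using non-pregnancy diagnostic criteria". Blood collections requires at least 10 hours of fasting for the OGTT and adds: "The participants complete all the other study assessments during the 2-hour waiting time". Table 3 places the lifestyle, IPAQ, depression and breastfeeding/contraception forms at the same visit.

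The aim 4 paragraph of the statistical section describes a different source. Utilities for the health states come from the literature, while clinical risks come from the study and costs from the centers and the literature. It does not mention the SF-36.

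**The concern.** The place and circumstances in which a woman rates her own health depend on whether she had GDM. A woman with previous GDM answers while fasted, part-way through a glucose test at a diabetes re-evaluation, with several other forms to complete. Every other woman answers a mailed form. If setting affects the answers, or if women who return a mailed form differ from those who do not, the result would look like a quality-of-life difference due to GDM. If the SF-36 scores are then turned into QALYs, that error would enter the aim 4 result.

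**Working it through.** **1. Is setting separable from GDM status?** Take a model with an intercept, an indicator for GDM and an indicator for the clinic route. As planned, every woman with GDM has clinic = 1 and every other woman has clinic = 0. The last two columns are identical, so the design matrix has rank 2 of 3. Only the sum of the GDM effect and the setting effect can be estimated. Covariates do not help, because no woman with GDM uses the mail and no other woman uses the clinic.

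**2. Group sizes**, from Power calculation and statistical analyses (2563 enrolled, 5% excluded for overt diabetes, 12.4% GDM):
- analysed: 2563 × 0.95 = 2435
- GDM, clinic route: 2435 × 0.124 = 302
- no GDM, postal route: 2435 − 302 = 2133

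The 302 assumes that every woman with GDM attends visit 3. The 2563 × 0.05 = 128 women with expected overt diabetes also count among the other participants who get the mailing, so they must be left out for the postal group to be free of diabetes.

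**3. How large would a setting effect have to be to matter?** The document gives no SF-36 figure, so this is a what-if. Assume no true GDM difference and a pure setting shift of d standard deviations. Use a two-sided 5% normal approximation (the protocol's general rule for continuous variables is the Mann–Whitney test).

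SE in SD units = √(1/302 + 1/n):
- n = 2133 (all mailed forms returned): 0.0615
- n = 1067 (half returned, assumed): 0.0652

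P(reject) = Φ(d/SE − 1.96) + Φ(−d/SE − 1.96)

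| Assumed d (SD) | All returned | Half returned |
|---|---|---|
| 0 | 5% | 5% |
| 0.05 | 13% | 12% |
| 0.10 | 37% | 34% |
| 0.15 | 68% | 63% |
| 0.20 | 90% | 87% |

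The smallest difference detectable with 80% power is (1.96 + 0.84) × SE, or 0.17–0.18 SD. A setting effect of that size could produce a finding or hide one.

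On a utility scale with an assumed SD of 0.12, the SE is 0.12 × 0.0615 = 0.0074 (0.0078 at half return). An assumed shift of 0.02 is then declared significant in 72–77% of studies. With SDs from 0.10 to 0.15 the range is 53–90%.

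**4. Does it reach the cost per QALY?** The SF-36 paragraph says the form is used for QALYs. The aim 4 paragraph builds QALYs from literature utilities and time in each state. If the first governs, the confounding enters aim 4. If the second governs alone, it does not. The article does not say how the two fit together.

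**5. What does the score measure?** It is taken once, three months after delivery, and the Background notes: "Shortly after the delivery the glucose values are generally restored to normal". It describes postpartum health and does not measure health while GDM is present.

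**The case against.** The form is self-administered in both groups, with the same instrument at about the same time after delivery. Only the place and the accompanying forms differ, and even completion at home is inferred from the mailing. Using an existing visit for those who attend and the mail for those who do not is a practical choice for one questionnaire supporting an exploratory aim. This lowers the likely size of a setting effect. It does not make the effect estimable.

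Three stronger readings are tempting, and the document does not support them:
- **That the cost per QALY is biased.** The only description of the economic analysis takes utilities from the literature. The path from the SF-36 to the aim 4 result is stated in one place and absent from the other, so it is conditional.
- **That prior health cannot be separated from GDM either.** No earlier SF-36 exists, but socio-economic data and BMI from visit 1, and the CES-D and IPAQ from visit 2b, allow partial adjustment. Only setting is fully tied to GDM status.
- **That the rejection percentages show a bias.** The SD, the shifts and the return rate are all assumed, and no SF-36 test is specifically planned. The figures show only that in a sample this large a modest effect, if present, would be taken for a GDM effect. They do not measure error in the cost per QALY.

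It could also be said that a condensed article leaves detail to fuller documents. That does not apply to the route, which the article states outright for both groups and which later analysis cannot repair.

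**Conclusion.** The point holds for the SF-36 comparison. As planned, any effect of setting or of differential non-response is inseparable from a GDM difference in the score, with about 302 women on one route and 2133 on the other under the protocol's own rates. This follows from the stated routes and needs no numerical assumption. It also relies on reading the article's sentence on the 2-hour wait as applying to visit 3, which the preceding sentence about breastfeeding at visit 3 supports.

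The size of any bias is unknown. Under assumed setting effects of 0.05 to 0.20 SD, a spurious GDM difference would be declared in about 12% to 90% of studies. The consequence for aim 4 depends on reconciling the SF-36 paragraph with the aim 4 paragraph. The lack of an earlier SF-36 is a lesser weakness that existing data partly cover.

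**What to change.** 1. Mail the SF-36 to all participants in the same window around three months postpartum, for completion at home. Women with GDM complete it before visit 3 and may hand it in there; it is not filled in during the OGTT.
2. State which utility source, SF-36 or literature, feeds the base case, and make the SF-36 and aim 4 paragraphs agree.
3. Describe the SF-36 score as postpartum health only.
4. Align the study-end wording with the mailing. For women without GDM, Study cohort says "the study will end when women and the baby leave the hospital after the delivery", yet they are sent a form three months later.

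The mailing already exists, so the cost is postage for about 300 more women. The downside is possible home non-response among women with GDM, which collection at visit 3 limits. Return rates should be reported by group.

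I would not add an SF-36 at visit 2b to serve as a baseline. Women with early GDM are not part of the 24–28 week screening, visit 2b is itself an OGTT setting, and GDM may already be present by then, so adjusting for that score could remove part of any effect.

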### Outcomes of the study

#### The diagnosis of GDM

Diabetes and GDM in early pregnancy are resp. defined as diabetes and prediabetes outside pregnancy [23]. The diagnosis of GDM between 24–28 weeks of pregnancy is based on the IADPSG criteria [9]. For women with a diagnosis of diabetes or GDM, data on the treatment and glycemic control will be collected at each visit with the diabetes nurse, dietician and/or diabetologist. The following data are collected: whether glycaemic targets are met or not, when and why insulin is started and changes in the dose of insulin. All concomitant medication and/or supplements will also be recorded.

#### Pregnancy and delivery outcome data

• *Maternal data* that are prospectively collected are: pregnancy duration, preeclampsia (de novo BP ≥140/90 mmHg > 20 weeks with proteinuria or signs of end-organ dysfunction), eclampsia, HELLP syndrome (according to the Tenessee criteria) [36], gestational hypertension (de novo BP ≥140/90 mmHg > 20 weeks), preexisting hypertension, pregnancy-induced cholestasis, ultrasound data on the presence of hydramnios (amniotic fluid index >25 cm), abdominal circumference ≥ P95 and estimated fetal weight ≥ P90 or ≤ P10.

• *Delivery data* that are prospectively collected are: type of labor (spontaneous, induced or caesarean before labor) and the indications if appropriate, type of delivery (spontaneous vaginal, forceps or vacuum, caesarean section during labor or planned caesarean section) and the indications if appropriate.

• *Neonatal data* that are prospectively collected are: macrosomia (>4 Kg), LGA (birth weight >90 percentile according to standardized Flemish birth charts adjusted for sex of the baby and parity), small for gestational age (birth weight <10 percentile according to standardized Flemish birth charts adjusted for sex of the baby and parity), preterm delivery (<37 completed weeks), 1 and 5 min Apgar score, shoulder dystocia, birth trauma, neonatal respiratory distress syndrome, congenital anomalies, neonatal hypoglycaemia, neonatal jaundice, hypocalcaemia, hypomagnesemia, polycythaemia and duration and indication for admission on the neonatal intensive care unit. Neonatal blood analyses are only done if there is a clinical warning sign in accordance with local practice.

Researchers are asked to evaluate whether the main reason of the maternal and neonatal complications and management is related to diabetes or GDM.

### Other study measurements

#### Evaluation of insulin sensitivity and beta-cell function during pregnancy and postpartum based on the OGTT

At the three visits blood samples are taken to later determine HbA1c and insulin (fasting and at the different time frames of the 75 g OGTT). These analyses will be performed in all women with diabetes or GDM and in a control group of women without diabetes or GDM. Analyses will be performed at the central lab of UZ Leuven. HbA1c is measured by reversed-phase cation-exchange chromatography (ADAMS HA-8160, Menarini Diagnostics Benelux, Zaventem, Belgium). Plasma glucose is measured by an automated colorimetric-enzymatic method (hexokinase-glucose-6-phosphate-dehydrogenase, application 668) on a Hitachi/Roche-Modular P analyzer. Insulin is measured by the immunometric ECLIA (Roche Modular E170, Basel, Switserland).

Glycaemia will be assessed by the area under the glucose curve during the OGTT, calculated using the trapezoidal rule. Insulin sensitivity will be measured using the insulin sensitivity index of Matsuda and DeFronzo [37]. Beta-cell function will be assessed by the insulinogenic index dived by HOMA-IR [38]. The insulinogenic index will be calculated as the incremental change in insulin concentration during the first 30 min of the OGTT divided by the incremental change in glucose during the same period [39,40]. As a measure of beta-cell compensation, the insulin secretion sensitivity index (ISSI-2) will be measured [41,42]. All these measures are validated for use in pregnancy.

